### 3. OBJECTIVES

Objectives:

- To assess whether *mCR* programmes result in better sustained effects on physical, mental and social outcomes in elderly patients not opting for regular CR, than patients who do not follow the *mCR* programme.
- To assess whether *mCR* as alternative for a regular CR programme is an effective means to increase participation and adherence of elderly in a CR programme.
- To analyse the induced costs of the *mCR* programme and determine its cost effectiveness.

Main outcomes include:

- Physical fitness: difference in  $VO_{2peak}$  (T1-T0), (T2-T0) and (T2-T1)
- Traditional risk factors for CVD
- MACE
- General health
- Care utilisation
- Costs of care utilisation
- Adherence
- Compliance

The primary hypothesis of the study is that joining the *mCR* programme results in a greater difference in  $VO_{2peak}$  in cardiac patients between T1-T0 and T2-T0 than not joining the *mCR* programme.

The second hypothesis of the study is that joining the *mCR* programme results in an equal or greater difference in  $VO_{2peak}$  in cardiac patients between T2 and T1 than not joining the *mCR* programme.

The third hypothesis of the study is that the joining the *mCR* programme results in improved traditional risk profile (i.e. lipid profile, HbA1C, lean body mass, blood pressure) in cardiac patients in comparison to not joining the *mCR* programme after 6 (T1) and 12 months (T2).

The fourth hypothesis of the study is that the overall occurrence of MACE (cardiovascular mortality, all-cause mortality, near sudden cardiac death, acute coronary syndrome, CV

intervention/surgery, CV hospital admission, CV emergency visit) in the intervention group is lower than in the control group after T1 and T2.

The fifth hypothesis of the study is that joining the *mCR* programme results in an improved general health (e.g. quality of life (SF-36v2: Physical and Mental Component Summary Score), level of depression (PHQ-9), level of anxiety (GAD-7) and dietary pattern (Mediterranean Diet Score)) in comparison to not joining the *mCR* programme after T1 and T2 in cardiac patients.

The sixth hypothesis of the study is that utilisation of care in the intervention group is lower than in the control group throughout the study period.

The seventh hypothesis of the study is that the costs of care utilisation in the intervention group are lower than in the control group throughout the study period.

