#### Secondary study endpoints/outcome

- Difference in  $VO_{2peak}$  from an incremental exercise test (T2-T0, T2-T1)
- Traditional risk factors:
  - Changes in lipid profile (T1-T0, T2-T0, T2-T1)
  - Changes in HbA1C (T1-T0, T2-T0, T2-T1)
  - Changes in renal function (T1-T0, T2-T0, T2-T1)
  - Changes in lean body mass (T1-T0, T2-T0, T2-T1)
  - Changes in blood pressure (T1-T0, T2-T0, T2-T1)
  - Changes in smoking habit (T2-T0)
- MACE: the occurrence of events (cardiovascular (CV) mortality, all-cause mortality, near sudden cardiac death, ACS, CV intervention/surgery, CV hospital admission, CV emergency visits) as composite endpoint (T2-T0) are registered and collected by monthly telephone calls.
- General health:
  - Difference in depression score assessed by: PHQ-9 questionnaire (T1-T0, T2-T0, T2-T1)
  - Difference in anxiety score assessed by GAD-7 questionnaire (T1-T0, T2-T0, T2-T1)
  - Quality of Life: SF-36v2, difference in Physical Component Summary Score and Mental Component Summary Score (T1-T0, T2-T0, T2-T1)
  - Difference in dietary pattern (reflected by total score and score on individual components) assessed by Mediterranean Diet Score (T1-T0, T2-T0, T2-T1)
- Care utilisation as composite endpoint of: (number of) admissions, emergency visits and cardiac interventions (PCI, CABG) (T2-T0).
- Costs of care utilisation based on activities (clinical admission days, emergency and outpatient clinic visits, GP visits for cardiac (related) complaints or issues, radiology/cardiophysiology/nuclear and laboratory tests,

and cardiac interventions) registered at T0, T1 and T2 and collected by monthly telephone calls with the participants between T1 and T2.

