## **10. Study objective 6**

Utilisation of care in the intervention group is lower than in the control group throughout the study period.

Differences between intervention groups in utilisation of medical care will be tested by linear mixed models with centre as random effect for continuous outcome or mixed models for logistic regression for dichotomous outcomes. When necessary continuous outcome variables will be transformed to obtain a normal distribution.

[figure not shown]

## 11. Study objective 7

To investigate the thesis that the costs of care utilisation in the intervention group are lower than in the control group throughout the study period.

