### *Health care cost estimation:*

Direct costs for mobile cardiac rehabilitation will be assigned for the intervention group (with telemonitoring guidance), but not for the control group (no intervention). Care utilization based on activities (clinical admission days, emergency and outpatient clinic visits, GP visits for cardiac (related) complaints or issues, radiology/cardio physiology/nuclear and laboratory tests, and cardiac interventions) will be registered at T1 and T2 and collected by monthly telephone calls with the participants between T1 and T2. A price will be assigned to each service and summed up for each patient individually:

|                                   | Mobile CR | control |
|-----------------------------------|------------------|----------------|
| Costs for CR               | Yes              | No             |
| Costs for care utilization | Yes              | Yes            |

Therefore, total costs (= TC) per patient comprise:

1. Costs for telemonitoring guidance (= CCR, only intervention group)
2. Sum of costs for medical services used outside CR (care utilization, = CCU).

Linear mixed models with centre as random effect will test differences between intervention and control group regarding total costs of care utilisation (see also section 5.1).

Additionally, incremental cost effectiveness ratios (ICER) defined as

$$\frac{\text{Total costs mobile CR} - \text{Total costs control group}}{\text{Outcome mobile CR} - \text{Outcome control group}}$$

will be estimated and a 95% confidence interval will be calculated. Outcome refers especially to the change of peak VO2 and Quality of Life (measured by Physical Component Summary Score and Mental Component Summary Score) during the follow-up period.

[figure not shown]

## 12. Study objective 8

Cardiac patients randomised to the *mCR* programme comply with the use of the smartphone (use of the smartphone on at least 4 days per week with a minimum of 30 minutes of activity per day with a total registration of 150 minutes of activity per week during 21 weeks) during the first 6 months of the study.

Descriptive statistics will be utilised to obtain insight in the use of the smartphone during the first six months of the study. Listed below are the parameters that will be determined.

- Total time (in hours) use of physical activity monitor
- Total time (in hours) use of physical activity monitor with light to moderate intensity

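### SAP section 11 does not say which cost variable tests objective 7; on the likelier reading it adds the mCR programme cost to one arm and so does not test the care-cost hypothesis

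*Combined protocol and SAP*

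**What the plan says.** **Hypothesis.** Protocol section 3: "The seventh hypothesis of the study is that the costs of care utilisation in the intervention group are lower than in the control group". SAP section 2.7 repeats this, and SAP section 11 opens with "To investigate the thesis that the costs of care utilisation in the intervention group are lower than in the control group throughout the study period".

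**Endpoint.** Protocol section 7.2.1 builds care-utilisation costs from medical activities: admission days, emergency, outpatient and GP visits, diagnostic and laboratory tests, and cardiac interventions. The mCR programme is not in that list.

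**Cost variables.** SAP section 11 (health care cost estimation) charges the programme to one arm: "Direct costs for mobile cardiac rehabilitation will be assigned for the intervention group (with telemonitoring guidance), but not for the control group (no intervention"). It continues, "Therefore, total costs (= TC) per patient comprise", and lists two parts. The first is "Costs for telemonitoring guidance (= CCR, only intervention group"). The second is the cost of medical services used outside CR, labelled CCU.

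**Test.** The only between-arm cost test named in that section is that linear mixed models with centre as a random effect "will test differences between intervention and control group regarding total costs of care utilisation". No symbol is given. The ICER that follows uses total costs in its numerator.

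**Declared changes.** SAP section 18 reports only the added per-protocol set. It declares no move from care-utilisation costs to total costs.

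**The concern.** The hypothesis is about CCU. The test is described by a phrase whose first half is the name just given to TC and whose second half is the name just given to CCU. An analyst who takes it as TC tests a different null hypothesis, because CCR is positive in one arm and zero in the other.

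Two things are at stake. If mCR does reduce care costs, CCR offsets part or all of that saving in TC, and the trial may fail to show it. If mCR leaves care costs unchanged, TC may come out significantly higher with mCR. Reported under objective 7, that result would read as if care use had become dearer.

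SAP section 16 divides the analyses among four beneficiaries and the CRO, so an outcome left open could be settled differently by different analysts, or after the data have been seen.

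**Working it through.** **Inputs from the documents.** Two-sided alpha 0.05 (protocol 9.1). 119 randomised per arm, and 83 per arm after the 30% withdrawal allowance (protocol 5.4, SAP 3). The allowance reproduces: 83 / (1 − 0.30) = 118.6, rounded up to 119. Protocol 7.9 and 7.10 follow withdrawn patients for utilisation of care, so the number with cost data may lie between 83 and 119.

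**Inputs that are assumed.** The documents give no programme price, no cost SD and no cost power, so there is no planned cost figure to reproduce. Write r = CCR/SD(CCU) and s = true saving in CCU divided by SD(CCU). I take r from 0 to 0.5, CCR the same for every mCR patient, and s = 0 or 0.45.

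**What each test estimates** (mCR minus control):
- on CCU: −s, in SD units;
- on TC: r − s, in SD units.

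With s = 0 the TC difference is r, above zero for any positive programme cost. It is zero only when the care saving exactly equals CCR.

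**Formula.** Two-sample t-test with n per arm, noncentrality λ = (r − s) × √(n/2), 2n − 2 degrees of freedom, critical value about 1.97. The random centre effect is ignored. For n = 119, √(119/2) = 7.714; for n = 83, √(83/2) = 6.442.

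**Case 1: a true care saving of 0.45 SD.** Probability of a significantly lower cost with mCR:

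| r | λ at 119 | Power, 119 per arm | Power, 83 per arm |
|---|---|---|---|
| 0 (same as testing CCU) | −0.45 × 7.714 = −3.47 | 93% | 82% |
| 0.05 | −0.40 × 7.714 = −3.09 | 87% | 73% |
| 0.1 | −0.35 × 7.714 = −2.70 | 77% | 61% |
| 0.2 | −0.25 × 7.714 = −1.93 | 48% | 36% |
| 0.3 | −0.15 × 7.714 = −1.16 | 21% | 16% |
| 0.45 | 0 | 2.5% | 2.5% |

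**Case 2: care costs equal in both arms (s = 0).** Probability that TC is significantly higher with mCR:

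| r | 119 per arm | 83 per arm |
|---|---|---|
| 0 (same as testing CCU) | 2.5% | 2.5% |
| 0.05 | 6% | 5% |
| 0.1 | 12% | 9% |
| 0.2 | 34% | 25% |
| 0.3 | 63% | 48% |
| 0.5 | 97% | 89% |

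**Sensitivity to scale.** SAP section 11 refers to section 5.1, which allows the outcome to be transformed. With lognormal CCU (assumed CV 1.5), r = 0.2, equal care costs and 83 per arm, 5,000 simulated trials gave TC significantly higher with mCR in 32% on the raw scale and 97% on the log scale. A fixed amount added to a skewed cost weighs more after a log transform.

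**The case against.** **The sentence may mean CCU.** The SAP calls CCU a sum of costs for care utilisation, so the total of those costs can be that same sum, which would match objective 7. This stands as a possible reading. A reader might infer that the SAP definitely tests TC, but the mixed label does not establish that. TC is likelier because it is defined immediately before the test and used in the ICER immediately after. The separate SAP definitions document, not available here, might settle the matter.

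**A CCU comparison may already be planned.** Protocol 9.1 describes care-utilisation costs by arm and plans t-tests on continuous variables at 6 and 12 months. Protocol 9.3 applies repeated-measures models to any outcome measure. SAP 1.1 takes the protocol as its primary source. It would therefore be too strong to say that nothing in the documents compares CCU. What stands is that these are general provisions and that SAP section 11, the specific plan for objective 7, names no such comparison. Objective 6 tests utilisation, not its cost.

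**A significant TC result is not an error.** A reader might take Case 2 as an inflated type I error or a rejection in the wrong direction. It is neither: with equal care costs and CCR above zero, total costs really are higher with mCR. The TC test is also conservative for the hoped-for claim, because with equal care costs the chance of a false finding of lower cost drops below 2.5%. Net cost is itself a stated aim (protocol 3, SAP 1.3). The harm arises only when TC is used to decide hypothesis 7.

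**The ratio could be small.** The programme consists of a loaned phone and heart-rate monitor, returned at 6 months, and about ten calls (protocol 6.1), whereas CCU includes admissions and interventions. Ratios of 0.1 or less are not excluded, so the upper rows of the tables should not determine how seriously the point is taken.

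**Conclusion.** The outcome of the objective 7 test is not identified and, on the likelier reading, does not match the hypothesis. That mismatch holds for any positive programme cost; its size depends on CCR/SD(CCU), which the documents do not give.

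If the ratio is 0.1 to 0.3 and the true saving is 0.45 SD, power at 119 per arm falls from about 93% to between 77% and 21%. At a ratio of 0.05 it is 87%, a modest loss. All these figures are conditional on the TC reading, on the assumed ratio and saving, and on a t-test that ignores centre.

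It would go too far to conclude that objective 7 cannot be answered. CCU has to be calculated for each patient in order to form TC, so the data will exist. Including CCR in the ICER is correct. This is a secondary objective with no cost-based sample size, and the point is worth correcting because the correction is specific and nearly free.

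**What to change.** In SAP section 11:
- name per-patient CCU, with the content given in protocol 7.2.1, as the outcome of the objective 7 test, and base the conclusion on hypothesis 7 on that result alone;
- report TC = CCR + CCU as a separately labelled net-cost comparison and keep it as the ICER numerator.

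The cost is a change of wording and one extra model. No new data are needed and the ICER does not change. The downside is that two cost results must be explained, and they may point in different directions.

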#### 13.1 Identifying variables influencing participation and analysing participation rates

Social, psychological, motivational, contextual and medical variables will be incorporated. All registered variables will be taken into account, predictors of participation and non-participation will be identified with multivariable models (multiple logistic regression analysis). Differences between European regions, different programmes and ages will be studied.

Statistical modelling of participation (to know the relative weight of different variables and how they can be combined to maximize the real interest on patients). This would also imply identifying the profiles or targets in which the pervasiveness of the program can be higher and, on the contrary, those targets or situations in which resistances or barriers may be greater.

[figure not shown]

Three complementary strategies are proposed to reach the objective 9:

#### **13.1.1. Strategy 1**

A literature review searching the possible explanatory or moderator variables of participation, from the strictly medical ones, to sociodemographic ones, united to the psychosocial variables (like the awareness of own health status, the locus of control, expectations, motivation, mood state, self-esteem, family support, quality of life). See *Ruano-Ravina A et al. Participation and adherence to cardiac rehabilitation programs. A systematic review. Int J Cardiol. 2016;223:436-443. doi: 10.1016/j.ijcard.2016.08.120*

#### **13.1.2. Strategy 2**

A qualitative study, with Focus Groups and individual interviews to current users as well as potential users, health professionals (from primary care and cardiology services). It allows us not only to know the attitudes and perceptions about the program, but also to identify participation resistances or barriers. At the same time it provides us possible keys in terms of communication which should be used to increase the value of the program, making it more attractive for the potential users.

#### **13.1.3. Strategy 3**

A quantitative study. We propose to estimate the probability of participation in the RCT according to different variables collected in participants and non-participants. We will perform firstly a descriptive univariate analysis of the included variables followed by logistic regression models. Bivariate analysis will compare the characteristics of participants in CR programs with non-participants. To compare these characteristics we will use Pearson's ji squared test or Mann-Whitney's U as appropriate.

We will perform different logistic regression models were the dependent variable will be participation or not. As independent variables we are going to use information collected in screened participants and grouped in different areas (see potential predictors for participation). We aim to include the maximum number of variables to try to explain participation and identify which characteristics are more tightly linked with participation. We will not use automatic procedures for the inclusion of variables in the models. The results will be expressed as odds ratios (OR) with 95% confidence interval (95%CI). For all models, we will calculate the Hosmer-Lemeshow calibration test and the C index. We

[figure not shown]

will compare the performance of the models using receiver operating characteristic (ROC) curves. We will select the model with the highest C index but including a low number of variables (looking for a parsimonious model explaining participation with the lowest number of covariates). This will enable the identification of patients more reluctant to participate and perform a more active information on them.

*Potential predictors for participation*

- Reason for not accepting cardiac rehabilitation (see "EU-CaRE & EU-CaRE RCT SAP definitions")

Socio-economic characteristics:

- Regular CR programme totally covered by health insurance

Socio-demographic variables:

- Country
- Geographical region
- Age
- Gender
- Ethnicity
- Educational attainment
- Employment status
- Currently involved in volunteer work (Yes, No)
- Co-habitation
- CR programme covered by health insurance
- Specify Totally covered Partially covered
- Urban/rural
- Number of kilometres from home to rehabilitation centre
- Number of kilometres from home to clinic
- Number of kilometres from home to general practitioner
- Index event
- Time lapse from index event to T0 CPET
- Symptoms (CCS & NYHA class)
- Medication use T0
- CVD risk factors prior to index event (smoker, diabetes mellitus type I/II, hypercholesterolemia, hypertension, family history CVD, physical activity prior to

[figure not shown]

index event, number of alcoholic units per week/number of days with alcoholic consumption)

- Co-morbidity (Previous ACS, PTCA/PCI or CABG, chronic heart failure, valvular heart disease, chronic/persistent atrial fibrillation, COPD, OSA, TIA/CVA, rheumatoid arthritis, nephropathy, peripheral artery disease, current depression)

As an exploratory analysis we will perform a separate analysis by recruitment centre to detect possible differences in models explaining participation according to different patient's characteristics.

Additionally the following analyses will be considered

- Structural Equation Models (3 Dependent Variables: interest and confidence in the program and expectations fulfilment).
- Cluster Analysis to identify and characterize different profiles of potential users and link them to the interest level in the program.

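### SAP 13.1.3 picks and describes the participation model by a C index from its own fitting data, with no numeric limit on variables and no optimism correction, so spurious predictors are likely

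*Combined protocol and SAP*

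**What the plan says.** SAP Section 13.1.3 (Strategy 3 of objective 9) fits several logistic regressions with participation as the outcome. On breadth it states: "We aim to include the maximum number of variables to try to explain participation". On how variables enter, it says only what will not be done: "We will not use automatic procedures for the inclusion of variables in the models". On performance: "For all models, we will calculate the Hosmer-Lemeshow calibration test and the C index"; models are also compared by ROC curves. The choice between models is then: "We will select the model with the highest C index but including a low number of variables", explained as "looking for a parsimonious model explaining participation with the lowest number of covariates". Results are odds ratios with 95% intervals, and the chosen model is meant to help identify patients who are reluctant to take part.

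The potential predictors listed in that section come to about 42 items, more after dummy coding. The section lists predictors, not models. Nothing in Section 13 mentions a bootstrap, cross-validation, hold-out sample, shrinkage, penalty or maximum number of parameters. For centres it adds: "As an exploratory analysis we will perform a separate analysis by recruitment centre". The pooled model carries no such label.

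**The concern.** A C index computed on the data that produced the coefficients overstates how well the model separates participants from non-participants. It also tends to rise when an unrelated variable is added. If it is used both to choose the model and to describe it, the overstatement enters twice: through fitting, and through picking the winner of several fits. A preference for few variables pulls the other way, but with no stated trade-off between size and C it cannot be applied in a repeatable way. The Hosmer-Lemeshow test on the same data is a weak safeguard, because a maximum-likelihood logistic fit has a calibration slope of exactly 1 in its own data.

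At stake is the quantitative part of objective 9. A C index and odds ratios that will not hold in new patients would be used to say who is reluctant to participate.

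**Working it through.** The SAP gives no figure for the participation model, so there is none to reproduce. The check asks what the rule would yield if no variable were related to participation.

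**Inputs**
- Participants: 238 (SAP 1.4 and 3).
- Non-participants: not in the documents; assumed 120, 238, 500 and 1000.
- Candidate terms: 40, close to the listed count; simulated as independent noise, half binary and half continuous.
- Size of a parsimonious model: not stated; assumed 5 variables.
- Number of models compared: not stated; assumed 20.
- Interval level: 95% (SAP 13.1.3).

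**Method.** Logistic maximum likelihood. C is the proportion of participant/non-participant pairs in which the participant has the higher fitted value. It is computed in the fitting data (apparent) and in a fresh sample of the same size.

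**Step 1. Apparent C with noise only** (means over 200 data sets)

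| Non-participants | 1 term | 5 | 10 | 20 | 40 | 40 terms, new sample |
|---|---|---|---|---|---|---|
| 120 | 0.522 | 0.569 | 0.598 | 0.642 | 0.702 | 0.499 |
| 238 | 0.520 | 0.555 | 0.579 | 0.616 | 0.664 | 0.500 |
| 500 | 0.515 | 0.549 | 0.572 | 0.602 | 0.642 | 0.500 |
| 1000 | 0.515 | 0.545 | 0.563 | 0.589 | 0.628 | 0.499 |

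Optimism at 40 terms runs from 0.628 − 0.499 = 0.129 to 0.702 − 0.499 = 0.203. Adding an 11th noise variable raised apparent C in 76 to 79% of data sets, by 0.004 to 0.006 on average.

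**Step 2. Parsimony imposed at 5 variables**

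| Non-participants | One fixed model: apparent C | At least one 95% interval excluding 1 | Best C of 20 models: apparent C | At least one 95% interval excluding 1 |
|---|---|---|---|---|
| 238 | 0.554 | 18.0% | 0.586 | 71.5% |
| 500 | 0.547 | 23.3% | 0.575 | 74.5% |
| 1000 | 0.543 | 21.3% | 0.568 | 75.5% |

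New-sample C was 0.50 in every cell. The fixed-model rate agrees with theory: 1 − 0.95^5 = 0.226. Selection alone lifts apparent C by 0.586 − 0.554 = 0.032, 0.575 − 0.547 = 0.028 and 0.568 − 0.543 = 0.025.

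**Step 3. Precision.** The best-of-20 rates rest on 200 data sets each, so the standard error is about √(0.745 × 0.255 / 200) = 0.031. A second set of runs gave 73 to 81% for the best of 20 and about 19 to 27% for one fixed model. Taking both sets together: apparent C of about 0.57 to 0.61 for the chosen five-variable model, a false-predictor rate of roughly 72 to 81%, and about 18 to 27% without selection.

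Stepwise selection by C gave 83 to 92%. The SAP rules out automatic procedures, so that range is not used here.

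**The case against.** The strongest reply is that the SAP does not select on C alone. It wants few covariates, and a mean gain of 0.004 to 0.006 from one noise variable would not persuade anyone looking for a small model. A reader might infer that the rule drifts to the largest model; the text does not support that, and the 40-term figures show the optimism of the measure, not the expected result of the rule. This part of the objection stands. What it does not answer is Step 2: with size held at five variables, choosing the winner by apparent C still raises the false-predictor rate from about one in five to about three in four. The ban on automatic procedures does not help either, since it leaves open how variables will be chosen and how many models will be tried.

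Other stronger readings should also be set aside:
- **That the rule is bound to produce predictors where none exist.** The rate depends on the unstated number of models and is about 18 to 27% if one model is fixed.
- **That objective 9 rests on this model.** Section 13.1 names three complementary strategies, including a literature review and a qualitative study, and Section 13.2 adds adherence analyses.
- **That the same rule is reused in each centre.** The SAP says only that a separate, exploratory analysis will be done. With 238/6, or about 40, participants per centre and about as many candidate terms, it would be fragile, but this was not simulated.
- **That BIC in Sections 5.1 and 6 already supplies a penalty.** There it selects covariance structures, not predictors.

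Objective 9 is also outside the eight objectives listed in SAP Section 2, which limits the weight of the point.

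**Conclusion.** The concern holds in a limited form. As written, the C index that picks and reports the participation model is an in-sample figure, and neither the unquantified preference for few variables nor the ban on automatic selection cures its optimism. With no true predictors it would average about 0.63 to 0.70 for 40 terms and about 0.57 to 0.61 for the best of 20 five-variable models, against 0.50 in new patients. At least one spurious odds ratio would appear in roughly 72 to 81% of data sets in the second case.

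These sizes rest on assumed numbers of non-participants (120 to 1000 for the 40-term figures), 20 models, five variables per model and independent noise predictors. With real predictors, or fewer models, they would differ. That the C index is in-sample is inferred from the absence of any validation text in the SAP; the separate definitions document was not available. The primary VO2peak analysis is untouched.

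**What to change.** In SAP 13.1.3, before analysis:

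1. List the candidate models, or set a maximum number of parameters and a selection rule that can be repeated. Hand selection cannot be rerun in a bootstrap sample, so this comes first.
2. Select by bootstrap optimism-corrected C: apparent C minus the mean, over bootstrap samples, of (C in the bootstrap sample − C of that same model in the original data). Repeat the whole selection in each sample.
3. Report the corrected C and the calibration slope for the chosen model.
4. Label the selected model's odds ratios as exploratory, because correcting C does not correct their intervals for selection.
5. For the by-centre analysis, describe the overall model's performance in each centre and do not select a new model there.

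The cost is some SAP wording, agreement on the candidate models, and a short bootstrap program in R or SAS, both already named in Section 16. The reported C index will look less favourable.
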